| **Primary**  **Evaluation Criteria** | The primary endpoints are measures of the safety and reactogenicity of the vaccine as determined by:   1. Occurrence of solicited symptoms during a 7 day follow-up period after each vaccination (day of vaccination and 6 consecutives days) 2. • Occurrence of unsolicited symptoms during a 28 day follow-up period after each vaccination 3. • Occurrence of serious adverse events throughout the study period |
| **Secondary Evaluation Criteria** | 1. **Humoral response to vaccine antigens:**   Post vaccination levels of IgG, IgA and IgM, expressed in arbitrary units (ng/ml), relative to the pre-vaccination level (D0): D28/D0, D56/D0, D84/D0, D168/D0, and D365/D0.   1. **Cellular immune response to vaccine antigens:**   The number of cells producing IFNγ by Elispot expressed in number of spots /106 cells |
| **Exploratory Evaluation Criteria** | **To evaluate IgG ability to recognise the native protein on Merozoite by using WB**   - **Parasite inhibition by ADCI (SGI %) on D0, D84, D168 and D365. (only if isotype study shows the production of MSP3 specific cytophilic Abs in > 30% of volunteers)** |
| **Statistical Methods** | The analysis shall be descriptive  The final analysis is planned 1 month post Dose 3 to evaluate whether the safety GO/No GO criteria are met to proceed to a phase 2b in. An annex safety analysis will be performed at the end of the study, 9 months post Dose 3. |

| Study phases | Screening | Vaccination Phase (Double blind) | | | | | | | | | | Follow up (Single blind) | | |
| --- | --- | --- | --- | --- | --- | --- | --- | --- | --- | --- | --- | --- | --- | --- |
| Clinic Visit | **V1** | **V2** |  | **V3** | **V4** |  | **V5** | **V6** |  | **V7** | **V8** | **V9** |  | **V10** |
| **Home visits1** |  |  | **HV1-5** |  |  | **HV6-10** |  |  | **HV11-15** |  |  |  | **HV16-21** |  |
| **Trial Timelines (Days,)** | **D-28** | **D0** | **D1-D5** | **D6** | **D28** | D29-D35 | **D36** | **D56** | **D57-D62** | **D63** | **D84** | **D168** | **D196-D337** | **D365** |
| **Time Windows (Days)** |  |  4 D |  |  |  4 D |  |  |  4 D |  |  |  4 D |  7 D |  7 D |  14 D |
| **Study procedures** |  |  |  |  |  |  |  |  |  |  |  |  |  |  |
| Screening consent |  |  |  |  |  |  |  |  |  |  |  |  |  |  |
| Study Consent |  |  |  |  |  |  |  |  |  |  |  |  |  |  |
| Check of inclusion /non Inclusion Criteria |  |  |  |  |  |  |  |  |  |  |  |  |  |  |

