|  | **SCREENING** | | | | | | | **VACCINATION** | | | | | | | | | **LONG TERM SAFETY FOLLOW UP** | | |  |
|  |  | | | | | | | **DOUBLE-BLIND PHASE** | | | | | | | | | **SINGLE-BLIND PHASE** | | |  |
|  |  | | | | |  |  |  |  | |  | |  | |  | |  |  | |  |
| **BS;** Blood Sample. **Vacc;** Vaccination. | | | | | | | | | | | | | | | | | | | | |
|  | | | | | | | | | | | | | | | | | | | | |

- Double blind (observer blind, participant blind), randomized, controlled, dose escalation, Age de-escalation, phase Ib study
- One study centre,
- Two parallel groups
- Group 1: 23 subjects (15 subjects receiving MSP-3 vaccine 15 µg and 8 subjects receiving Hepatitis B vaccine).
- Group 2: 22 subjects (15 subjects receiving MSP-3 vaccine 30 µg and 7 subjects receiving Hepatitis B vaccine)
- Immunization schedule will be 0, 1, and 2 months for all cohorts and provisionally as following for each group:
  - Study days 0, 28 and 56 for group 1
  - Study days 14, 42, 70 for group 2
- Vaccinations of groups 1 and 2 will be staggered: immunization in group 2 will start 2 weeks after group 1. This interval may be extended if deemed necessary due to SAEs or other safety concerns.
- Randomization will be done for each group at the times of first vaccinations.
- Route of inoculation will be by subcutaneous injection into right or left deltoid (alternately).
- Each child will be observed for at least 60 minutes after vaccination to evaluate and treat any acute adverse events (AEs)
- Study duration will be approximately 13 months per subject.
- Seven (7) day follow-up period for solicited adverse events (day of vaccination plus 6 subsequent days)
- Twenty eight (28) day follow-up period for unsolicited adverse events (Vaccination day plus 27 subsequent days)
- Follow-up of serious adverse events (SAE’s) for 12 months after the first dose of study vaccine (9 months after dose 3)
- At the end of the follow-up period for unsolicited AEs (i.e., one month after the third dose), subjects will be followed by field workers at home at monthly intervals to record SAEs.
- Data collection: conventional Case Report Form (CRF).

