# Trial design and methodology

## Description and justification of design

The study is a single centre randomised controlled and blinded study (observer blind). It will be conducted at the CNRFP Vaccinology unit located in Balonghin. Children in the catchments area within the 1-2 years age group, whose parents consent will be screened to randomise 45 eligible participants.

Clinical, biological and immune response data gathered after vaccination with 15µg and 30µg MSP 3 LSP will be compared to:

- The children’s baseline data before vaccinations, and
- The post vaccination data of children in the control group.

Randomisation will ensure that the comparison groups are similar in relevant characteristics at baseline. The concealment of allocation before enrolment will further enforce the randomisation. Individuals who will make the assessment of the study end points will be completely blinded of the vaccine administered. This will ensure that there is no observer bias. Further, reporting or information bias will be minimised, because the recipients will also not be aware of which vaccine they have been administered. This is possible because the selected control vaccine has not been in routine use in this area, and has only now been recommended by the Ministry of Health. Cross over immunisation at the end of the trial will involve only those children who will received the study vaccine; they will be administered the control vaccine in the interest of public health benefits for them.

The schedule of vaccination at 0, 1 and 2 months has been adopted because it is suitable for the target group. The idea is to eventually deploy the vaccine through the expanded programme on immunisation should the vaccine become registered for public use. For the EPI age group, it is not only an efficient delivery mechanism, but they are also the most vulnerable group to malaria.

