### Method of blinding and breaking the study blind

Data pertaining to the trial will be collected in a double blinded (observer blinded) manner. “Double blinded (observer blinded)”in this context means that the vaccine recipient and their parent(s)/guardian(s) as well as those responsible for the evaluation of safety and immunogenicity endpoints will all be unaware the exact treatment, (MSP3 or Hepatitis B)given to the participant. The only study staff aware of the vaccine assignment for Hepatitis B or MSP3 will be those responsible for the storage and preparation of vaccines; these staff will play no other role in the study.

. Sealed envelopes labelled with the study ID number and containing the treatment allocated to each particular ID number will be provided to the investigator. The clinical investigator will only be allowed to open an envelope after ensuring that the child before him has met all eligibility criteria and has been given the study ID number. For each child, eligibility will have to be counter checked and signed by a second person before allocation of study ID number.

All envelopes will be retained to be checked by the clinical monitor.

The local safety monitor who is independent from the study team will also be provided a sealed randomisation list corresponding to each group. In total, 2 sealed randomisation list will be provided. If deemed necessary for reasons such as safety, the Local Safety Monitor in Ouagadougou as well as AMANET Central Safety will unblind the specific enrolled subject without revealing the study blind to the investigators.

As part of the safety monitoring plan, safety reports will be produced at 5 timepoints in the trial. An independent statistician will analyze the data, thereby maintaining the blind of the investigator group.

A formal reporting and analysis plan (RAP) will be developed. Once the study is completed and the database locked. AMANET will be responsible for initiating the execution of the statistical analysis plan in collaboration with the investigator team and breaking the blind.

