## Data processing

The principal investigator will review and approve of the CRF pages for data entry. The data base for this study is created in Microsoft Access® software and shall be entered by two separate data entrants. The supervising data manager will do all the data reconciliations and validations leading to the validated file for each participant. The database is designed to keep track of all entries in time and password and will be able to provide a complete audit trail.

Any illegible CRF entries will be sent back to the clinical investigators with accompanying appropriate data query form. The monitor will also routinely check the database against the CRFs, and will ensure that all accumulated data query resolutions are verified as consistent on the database, CRF and source document.

Regular reports will be compiled for presenting to the DSMB for their ongoing review of safety data. This shall be in a blinded manner. The final analysis will be done immediately after day 84 to allow for phase IIb study Go/No go evaluation.

At the end of the study, all data queries will be resolved, data cleaned and accepted before database locking. After database lock, no further entry shall be possible, and this is set for month 14.

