### Native protein recognition on Merozoite

Mature schizont-stage proteins of *P. falciparum* (3D7 clone) will be extracted in Laemmli sample buffer, submitted to electrophoresis, and transferred to nitrocellulose as described9 Nitrocellulose strips will then be incubated with each sera and the reaction revealed.

The intensity of the reactivity was classified as negative, positive (+), or strongly positive (++).

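### Two tables label follow-up after D84 single-blind while the text keeps assessors blinded to database lock, so late SAEs and Western blot grades could be judged with allocation known

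*Protocol*

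**What the plan says.** Two tables divide the trial by blinding status:

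- **Synopsis schedule.** V2 to V8 (D0 to D84) stand under "Vaccination Phase (Double blind)". V9 (D168), home visits 16 to 21 (D196 to D337) and V10 (D365) stand under "Follow up (Single blind)".
- **Section 3, design figure.** Long-term safety follow-up, with clinic visits at D168 and D365, is headed "SINGLE-BLIND PHASE".

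The text describes a blind with no such break:

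- **Section 4.1:** "Individuals who will make the assessment of the study end points will be completely blinded of the vaccine administered", with no end date.
- **Section 5.2.2:** "those responsible for the evaluation of safety and immunogenicity endpoints will all be unaware the exact treatment". Execution of the analysis plan and breaking of the blind are introduced by "Once the study is completed and the database locked".
- **Section 6.3:** "After database lock, no further entry shall be possible, and this is set for month 14".
- **Sections 12.1.3, 17.2 and 19:** allocation is revealed at the end of the study or, for cross-over immunisation, after the database freeze.

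Section 16.1 shows what the label means here. It calls the trial single-blinded to participants and treats double blinding as concealment from those who assess endpoints.

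**The concern.** A site cannot follow both instructions. If it follows the schedule, the clinicians who detect and attribute SAEs after D84 may know which vaccine each child received. SAEs are part of the primary evaluation criteria to the last visit, and sections 13.4.2.3 and 14.1 give the investigator the first judgement of causality. In a malaria vaccine trial, knowing the allocation can influence whether an admission is attributed to the vaccine.

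The late laboratory work is exposed too. D168 and D365 are two of the six serology days and two of the four Western blot and ADCI days. The synopsis also lists ELISPOT at D168. The Western blot is the most open to influence, because it is graded by eye: "The intensity of the reactivity was classified as negative, positive (+), or strongly positive" (section 15.3.1).

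The label changes where the go/no-go analysis falls. Section 6.3 places that analysis immediately after D84. Sections 5.2.2 and 5.2.10 assign an independent statistician to the DSMB safety reports, but the protocol does not extend that safeguard to the D84 analysis.

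**Working it through.** The protocol gives no figure for this exposure, so the check aligns the table headers with the visits and then counts days.

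**1. Where the phase starts.** In both tables D84 is the last visit under double blind and D168 the first under single blind. The protocol does not say on which side the days between D84 and D168 fall. Section 3 starts monthly home follow-up for SAEs one month after dose 3, which favours a start just after D84. Both readings are carried forward.

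**2. Share of SAE follow-up.** Section 3 follows SAEs for 12 months from the first dose, taken as 365 days.

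- Start at the end of D84: 365 − 84 = 281 days; 281/365 = 77%.
- Start at the D168 visit: 365 − 168 = 197 days; 197/365 = 54%.

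Counting from screening at D-28 (365 + 28 = 393 days) gives 281/393 = 72% and 197/393 = 50%.

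**3. Overlap with peak transmission.** The epidemiology section puts the peak at June to October: 30 + 31 + 31 + 30 + 31 = 153 days. Section 5.2.3 starts vaccination in March 2007, with the second group 14 days after the first. First doses are therefore assumed to run from 1 March to 14 April 2007 (31 March + 14 days).

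| Start of phase | First dose 1 March | First dose 14 April |
| --- | --- | --- |
| D84 falls on | 24 May | 7 July |
| Peak days from then to 31 October | 153 (100%) | 25 + 31 + 30 + 31 = 117 (76%) |
| D168 falls on | 16 August | 29 September |
| Peak days from then to 31 October | 16 + 30 + 31 = 77 (50%) | 2 + 31 = 33 (22%) |

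**4. What is not exposed.** Section 5.2.3 limits the go/no-go analysis to safety data one month after dose 3, all collected under double blind. Solicited events end within a week of each dose. Unsolicited events end 28 days after each dose in the synopsis (D84 for the third) and 30 days after dose 3 in the unsolicited-symptoms section (56 + 30 = D86). Two of the three primary components are therefore complete at, or within about two days of, D84. The third, SAEs, is exposed only in its later part.

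**5. A related definition.** The ATP safety cohort (section 16.3.1.2) requires an unbroken randomisation code, except for unblinding by the DSMB for safety analysis. If codes were opened to study staff for follow-up, the children concerned would not meet that criterion as written.

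**The case against.** The strongest reply is that the conflict lies in two header cells. The protocol does not unblind anyone at D84, name who would learn allocations or describe how. The text that governs unblinding says the opposite each time. This stands: a reader might infer from the label that the blind is lost at D84, and the documents do not support that. They support only that the label permits it.

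A reader might also infer that almost all of the malaria season is unblinded. That needs both the assumed dates and a start at D84. Counted from D168, at most half of the peak days are exposed, and even from D84 the low end is 76%.

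The likely damage is limited in other ways:

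- SAEs are defined largely by outcomes such as death and hospital admission. They are reportable whatever the investigator thinks of relatedness, and the sponsor also assesses causality.
- The analysis is descriptive, without comparison between groups (section 16.4).
- ELISA gives concentrations, ELISPOT spots are counted on a reader, and sample tubes carry an identification code. The plainly subjective reading, the Western blot, is exploratory.

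These points reduce the size of the problem but do not remove the contradiction. The label appears in two separate tables, so it is not a slip in one cell, and the term has a stated meaning in section 16.1. The definition of an SAE does not protect the causality judgement. A later analysis plan could guard the D84 analysis, but it cannot settle what the protocol tells the site about blinding.

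**Conclusion.** The protocol contradicts itself on blinding after the D84 visit. As written, the schedule and figure allow investigators to know allocation while detecting SAEs and judging their causality, and allow readers to know it when grading late assays, chiefly the Western blot. This can bias the annex safety analysis and those readings. It does not touch the go/no-go safety data.

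The exposed share of SAE follow-up is 54% if the phase starts at the D168 visit and 77% if it starts at the end of D84, counted from the first dose. On the assumed first doses of 1 March to 14 April 2007, that is 33 to 77 or 117 to 153 of the 153 peak-season days respectively. The conclusion that the text must be reconciled does not depend on either assumption. Whether anyone would in fact have been unblinded cannot be told from the documents.

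**What to change.** 1. In the synopsis schedule and the section 3 figure, replace single blind with observer-blind follow-up to D365, in line with section 5.2.2.
2. State that the independent statistician already used for the DSMB reports runs the D84 go/no-go analysis and releases group-level tables only.
3. State that investigators, field workers and assay readers stay blinded to individual allocation until the month-14 lock. The route in section 5.2.2 for unblinding a child for safety reasons is unchanged.
4. Withhold individual anti-HBs results from the same people until lock. Section 9.2 plans a sample six months after dose one to find children without protective levels, and these results could reveal who received hepatitis B vaccine.

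The cost is a wording amendment and an extension of the statistician's task, with no new visits or samples. The downside is that the investigator team sees individual allocations and anti-HBs results only after lock. Section 5.2.2 already places unblinding at that point, and section 9.2 already places revaccination at the end of the study.

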# Background Information

## Introduction

Among the four species of Plasmodium that cause human malaria, *P. falciparum* is responsible for most disease and death from malaria. Its life cycle is complex. Disease occurs as a result of the asexual blood stage when parasites invade and grow inside red blood cells. *P. falciparum* virulence is partially explained by its ability to use various receptor pathways to invade red blood cells of all ages. Red blood cells infected with *P. falciparum* bind to endothelium or placenta allowing the parasite to avoid spleen-dependent killing mechanisms but contributing much to pathogenesis1.

Anopheline mosquitoes inject sporozoites into the subcutaneous tissue and less frequently directly into the blood stream. The sporozoites then travel to the liver, where they invade hepatocytes. Under two weeks later, each infected hepatocytes releases 20,000-40,000 merozoites into the bloodstream. Despite the destruction of liver cells, no disease results from the infection during parasite development within hepatocytes. Only the blood stages of the infection produce clinical symptoms and malaria disease.

Red blood cells are invaded through a determined sequence. *P. falciparum* must engage receptors on red cells for binding2 and undergo apical reorientation, junction formation, and signaling3,4. The parasite then induces a vacuole derived from the red cell plasma membrane and enters the vacuole by a moving junction. Within this parasitophorous vacuole *P. falciparum* develops over 48 hours producing around 17-32 merozoites, each able to invade other red cells. Particular to *P. falciparum* is its ability to modify the surface of the red blood cell in a way that the infected cells can adhere to the vascular endothelium and other tissues, where they may cause disease. Parasite sequestration in various organs (brain, heart, liver, kidney and placenta) contributes to the pathogenesis of malarial disease.

Following a number of intra-erythrocytic cycles, a small proportion of asexual parasites convert to gametocytes that are critical for the transmission of the infection to others through female Anopheline mosquitoes. Gametocytes cause no disease and there is no known induced natural immune response to this intracellular sexual form of the parasite.

The strongest natural defence against this parasite is observed in exposed individuals from hyper-endemic malaria areas. Humans acquire a protective immunity, non-sterilizing and not dependant on the parasite strain. I*n vivo* transfer of immune African antibodies to non-protected, *P. falciparum* ridden individuals considerably reduces the level of parasites and protects these subjects5. Defence mechanisms studies show that these protective antibodies work in a “roundabout” way, through an antibody-dependant cellular inhibition mechanism (ADCI), which causes monocytes to offload parasitostatic substances. This mechanism, has only been observed with IgG1 and IgG3 cytophilic immunoglobulin isotypes, and is now considered a major stage in the acquisition of a protection against *P. falciparum* clinical malaria6, 7, and 8. Unfortunately, this natural immunity to malaria takes a long time, with repeated attacks to develop; and this makes the children born in endemic areas especially vulnerable to attacks of malaria.

With the apparent failure of current control measures as evidenced by the increasing burden of malaria, there is an urgent need to develop more tools for fighting the scourge of malaria. An effective vaccine against malaria would hold such a promise.

The vaccine strategy developed in this protocol is based on the observation of human *P. falciparum* interactions and consists of three steps: i) limited, ethically acceptable, clinical experiments in order to identify the immune mechanisms underlying *in vivo* clinical events, ii) *in vitro* experiments based on these mechanisms in order to identify target antigens, iii) *in vivo* studies in order to assess the role of these antigens in the protection acquired in humans.

The antibody-dependant cellular inhibition method (ADCI) was used as a mean of selecting molecules able to induce protective immunity to malaria. An antibody specific mechanism which promotes parasite killing mediated by monocytes was then identified in sera of clinically protected individuals. These antibodies are specific to the surface protein of the Merozoite (MSP3), a protein of 48kDa molecular weight9. Purified immunoglobulins from the protected individuals are confirmed to be efficient in ADCI and the ones that are specifically directed against MSP3 are mainly cytophilic. On the contrary, in the unprotected individuals whose antibodies are not ADCI effective, anti-MSP3 antibodies are essentially non-cytophilic10, 11.

The MSP3 region that induces ADCI effective antibodies was highlighted and its sequence defined (MSP3b). It contains an epitope that is not defined by a repetitive structure, and so seems to be non-polymorphic and well conserved. Antibodies induced in mice against this epitope, as well as human antibodies immuno-purified on this peptide, elicit a strong inhibition of *P. falciparum* growth in ADCI assay, whilst control antibodies, directed to peptides from other molecules, do not10, 11, 12. The correlation between isotypes of antibodies produced against the 48 kDa epitopes, clinical protection, and ability of specific anti-MSP3 antibodies to block the parasite schizogony in the ADCI assay suggested that this molecule is involved in eliciting protective mechanisms. Moreover, in contrast with other vaccine candidates, the target B and T-cell epitopes were found to be fully conserved in 67 *P.falciparum* isolates13.

